## **Methods**

This is a single-blinded, block-randomization controlled trial in a prospectively controlled laboratory. Sixty-six healthy university students will be recruited from the University of Sharjah, United Arab Emirates (UAE). The volunteers will be divided into three systemically randomized experimental groups. Each group will be admitted to a program of training utilizing one of three expert modes of the Russian current. The electrically elicited quadriceps muscle extensor torque

will be measured in response to modes at the participants' maximum tolerance at three points before the start of training, after three weeks of training, and at the six-week follow-up by the Biodex isokinetic system.

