## **Hypothesis**

We hypothesize that electrically induced torque of the quadriceps muscle in healthy persons will be differently affected by various Russian current modes.

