## **2.4 Study procedure and outcome measurement**

Before taking part in the study, all eligible volunteers will be given information about it and asked to sign an informed consent form before the stimulation session. Baseline assessment will include demographic information, and the MVIC will be collected prior to stimulation sessions. The evaluation of primary and secondary outcomes will take place at the end of the intervention, three weeks after randomization, and at the six-week follow-up. The flow of participants throughout the investigation is represented in Fig. 2.

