### **Primary outcome measure**

Considering the potential advantages of NMES for enhancing muscle performance and the dearth of research in this area, the main objective of this study will be directed to evaluate the impact of various Russian current expert modes on the maximum electrically induced torque of the quadriceps femoris, and to compare the electrically elicited knee extensor torque at the maximal stimulation tolerance level using 3 different RC experts' modes (off mode, on mode and on2 mode).

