## **2.7 Sample size calculation**

The sample size will be based on a pilot study considering quadriceps torque as a primary outcome. The required sample size was calculated by assuming 80% power with a significance level of 0.05. To detect the minimum mean difference of 1.5 points and a standard deviation of 2.5 and considering a 10% dropout is the most suitable. [25]

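### The primary torque comparison is assigned to both week 3 and week 6, with no primary time point and no deciding comparison, so the false-positive rate depends on a choice still open after the data are seen.

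*Protocol*

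**What the plan says.** - **Outcome.** The Protocol's Primary outcome measure paragraph (under 2.4) aims "to compare the electrically elicited knee extensor torque at the maximal stimulation tolerance level using 3 different RC" modes. It singles out no reference mode and no pair.
- **Timing.** Section 2.4 sets these times: "evaluation of primary and secondary outcomes will take place at the end of the intervention, three weeks after randomization, and at the six-week" mark. The abstract's Methods say torque is measured "at three points before the start of training, after three weeks of training, and at the six-week follow-up", and 2.10 also lists weeks 3 and 6. None of these places ranks one above the other.
- **Hypothesis.** It is non-directional: "electrically induced torque of the quadriceps muscle in healthy persons will be differently affected by various Russian current modes".
- **Error rate.** The only one given is in 2.7: "The required sample size was calculated by assuming 80% power with a significance level of 0.05". It is attached to a "minimum mean difference of 1.5 points and a standard deviation of 2.5", with no pair of modes and no time point.
- **Analysis.** Section 2.10 names descriptive statistics and Pearson correlation. It names no test between modes.

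**The concern.** Week 3 is the end of training and week 6 is three weeks after it. One measures the immediate effect and the other what is retained, and the two can disagree. The three pairs of modes can disagree as well. Because the hypothesis is satisfied by any difference in either direction, up to six contrasts (3 pairs × 2 times) could each be presented as its confirmation.

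If the deciding one is picked once results are visible, the stated 0.05 no longer describes the chance of a false claim. The Discussion hopes that the findings may help physiotherapists choose the most effective settings, so a chance difference could influence practice.

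**Working it through.** **Inputs from the Protocol.** Three arms; 66 participants (abstract, Methods), taken as 22 per arm because no allocation ratio is stated; alpha 0.05 (2.7), taken as two-sided; 10% dropout (2.7), giving 22 × 0.9 = 19.8, about 20 completers per arm; difference 1.5 and SD 2.5 (2.7).

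**Assumed.** Parallel arms, normal outcomes, and a within-person correlation ρ between week-3 and week-6 torque. The Protocol gives no ρ, so a range is shown.

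**Step 1: does the sample size reveal the deciding comparison?** The Protocol states no family-wise rate to reproduce, so 66 is the only figure to check.
- Two-arm contrast: n per arm = 2 × (2.5/1.5)² × (1.960 + 0.842)² = 43.6, so 44 per arm and 132 in total before dropout. This does not match 66.
- One-sample or paired formula: (2.5/1.5)² × (1.960 + 0.842)² = 21.8, so 22; 22 × 3 = 66. This matches, but it compares no two modes and includes no dropout.

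The intended comparison cannot be inferred from the sample size.

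**Step 2: false-positive rate by later choice.** Simulation with no true difference, 100,000 runs per scenario, 22 per arm, each test at two-sided 0.05:

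| ρ | Any of 3 pairs, one time | Any of 6 contrasts, both times | Overall F-test at each time, either counts |
|---|---|---|---|
| 0 | 12.1% | 22.8% | 9.6% |
| 0.3 | 12.1% | 22.0% | 9.5% |
| 0.5 | 12.1% | 21.4% | 9.2% |
| 0.7 | 12.3% | 19.8% | 8.6% |
| 0.9 | 12.3% | 17.0% | 7.3% |
| 0.95 | 12.3% | 15.5% | 6.6% |

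With 20 per arm the figures are nearly the same (21.5% for six contrasts at ρ = 0.5). One overall test at one time gives 5%.

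As a check, two independent tests give 1 − 0.95² = 9.75%, in line with the last column at ρ = 0. Six independent tests would give 1 − 0.95⁶ = 26.5%. The simulated 22.8% is lower because the three pairs share arms.

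**Step 3: power of one overall three-arm F-test at one time.** Noncentrality λ = n × Σ(μᵢ − μ̄)² / σ², with σ² = 6.25 and the largest difference between modes equal to 1.5.
- Third mode midway (0, 0.75, 1.5): Σ = 1.125. For n = 20, λ = 3.60 and power is 36%. For n = 22, λ = 3.96 and power is 39%.
- Two modes equal (0, 0, 1.5): Σ = 1.5. For n = 20, λ = 4.80 and power is 47%. For n = 22, λ = 5.28 and power is 51%.

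**The case against.** The strongest reply is that the Protocol plans no pairwise test. Section 2.10 names only descriptive statistics and correlation, and the 0.05 in 2.7 is a sample-size input, not a decision rule for six tests. The hypothesis is global, and one overall test, or one repeated-measures test covering both visits, would answer it at 5%. This stands. A reader might infer that the trial carries a 21% false-positive risk instead of 5%, but the documents do not support that as a fact. It requires all six contrasts to be tested unadjusted, with any one counting, and an assumed correlation of 0.5.

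A second reply is that alpha allocation and testing order commonly sit in a statistical analysis plan, which may exist but is not shown. This also stands, and their absence is no part of this point. It does not cover the primary time point and the deciding comparison. Those belong in the protocol, because the sample size depends on them, and here 2.4 itself assigns the primary outcome to two times.

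A third reply is that the statistician is blinded and the data are coded (2.6). This helps little. Under a non-directional hypothesis a significant contrast between two coded groups, at either visit, can be recognised and chosen without knowing which mode is which.

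Finally, 2.9 speaks of individuals undergoing three randomized test conditions, which can be read as within-person testing. The calculations follow the parallel groups of the abstract and 2.5. The missing time point and comparison do not depend on that reading.

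**Conclusion.** The point holds in a conditional form. The Protocol fixes neither a primary time point nor a deciding comparison for its primary outcome, and it states one significance level for one unnamed difference. That much is read directly from the text.

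The size depends on the analysis eventually chosen: 5% for a single overall test, about 7% to 10% for an overall test at each visit with either counting, and about 16% to 23% for six unadjusted contrasts. The ranges cover correlations from 0 to 0.95 and assume parallel arms of about 20 to 22, normal outcomes and two-sided tests. No single value in them can be called the trial's error rate. The defect is that the rate is left open and can be settled after the results are known. It should be corrected.

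**What to change.** In 2.4 and 2.10, before unblinding and preferably before any outcome data are analysed, name one primary comparison. One workable form:

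1. Primary: the overall three-arm test of electrically elicited torque at the end of training (week 3), two-sided 0.05.
2. Only if it is significant: the three pairwise mode differences at week 3, each at 0.05. With exactly three arms this is a closed procedure. If the modes are not all equal, at most one pair can still be truly equal, so the family-wise rate stays at 0.05 without further correction.
3. Week-6 torque becomes secondary. Discomfort stays the secondary outcome it already is.

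Week 3 is an example. If retention is the main question, week 6 could be primary instead, provided one is chosen in advance. Section 2.7 should then state which comparison and time point its difference refers to.

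The cost is a few sentences, with no added participants, visits or measurements. Two drawbacks should be accepted openly. A difference seen only at week 6, or only in one pair without a significant overall test, would no longer be confirmatory. And at the planned difference of 1.5 and SD of 2.5, the overall test has only about 36% to 51% power with 20 to 22 per arm, so at that effect the pairwise step would be reached about half the time at best.

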### **Primary outcome measure**

Considering the potential advantages of NMES for enhancing muscle performance and the dearth of research in this area, the main objective of this study will be directed to evaluate the impact of various Russian current expert modes on the maximum electrically induced torque of the quadriceps femoris, and to compare the electrically elicited knee extensor torque at the maximal stimulation tolerance level using 3 different RC experts' modes (off mode, on mode and on2 mode).

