# **The effect of different Russian Current parameters on maximum voluntary isometric contraction of the quadriceps muscle among University of Sharjah students: A study protocol for a randomized controlled trial**

## **Abstract**

**Background:** Neuromuscular electrical stimulation (NMES) is widely used in rehabilitation that stimulates the peripheral nerve to cause visible muscle contraction to strengthen weak muscles. Physiotherapists utilized a variety of electro-motor stimulation modalities to enhance muscle performance, muscle reeducation, decrease muscle spasticity, and postpone atrophy. One of the most well-known neuromuscular electrical stimulations is the Russian current, recommended for boosting muscle strength due to its high tolerance and low pain provocation. As individual NMES parameters have not been clearly evaluated in literature, independent evaluation of individual NMES parameters can provide clinically relevant information on how NMES might be optimized to promote strength muscle training in both healthy and afflicted subjects. Of interest, an example of a parameter that has not received significant attention is the expert mode.

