contraction, with 0 indicating "no pain" and 10 the "worst pain imaginable." Participants will be informed that a pain level of 7/10 is the maximal acceptable pain, If the pain rating reaches 7/10 or if they decide to discontinue testing for any other reason, the trials will be discontinued immediately. Similarly, the participants will be instructed to stop stimulation at a similar level of discomfort. Individuals will be submitted to the following 3 randomized test conditions, and the electrically RC elicited isometric knee extensor torque will be measured in response to each of the modes at the participants' maximum tolerance. RC stimulation session will last for 15 minutes. The Russian current neuromuscular electrical stimulation will be administered using a Chattanooga Forte 200 Combo stimulator (DJO Global, Vista, CA). The Russian currents produce 50 bursts per second at a carrier frequency of 2500 Hz, with each burst lasting 10 milliseconds and followed by a 10-millisecond inter-burst gap, resulting in a 50% duty cycle and a 200-microsecond phase duration as a fixed parameter. which automatically adjust the 3 expert modes:

OFF mode;

ON2mode; consists of two intervals the stimulus will be applied as; preset on the device, following by 2 second off and then and ON2 stimulus that has a frequency of 50 Hz and 100% amplitude.

Rest mode; consist of two intervals the stimulus will be applied as; preset on the device, then follow by a continuous Rest stimulus that has a frequency of 24 Hz and 83% amplitude.

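### The title asks about voluntary strength (MVIC), but the primary outcome is torque elicited with the modes being compared, so the plan as written does not isolate a training effect or answer the MVIC question

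*Protocol*

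**What the plan says.** **The question.** The title is "The effect of different Russian Current parameters on maximum voluntary isometric contraction of the quadriceps muscle", and the Impact paragraph of the abstract repeats the voluntary-contraction aim.

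**The outcome.** The primary objective in section 2.4 is "to compare the electrically elicited knee extensor torque at the maximal stimulation tolerance level", with the three modes as the things compared. Section 2.9 tells participants to relax during stimulation, so that none of the torque is voluntary.

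**The design.** The abstract (Methods) states: "Each group will be admitted to a program of training utilizing one of three expert modes of the Russian current". Section 2.5 randomises each participant to one mode.

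**When and how torque is measured.** On elicited torque, the same part of the abstract says that it "will be measured in response to modes at the participants' maximum tolerance at three points before the start of training, after three weeks of training". The third point is week 6. Section 2.4 places the outcome evaluations after the three weeks of training and at week 6. For baseline, section 2.4 names only demographic information and MVIC.

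**Test mode.** Section 2.9 puts individuals through three randomised test conditions and says that "the electrically RC elicited isometric knee extensor torque will be measured in response to each of the modes". No section fixes one test stimulus common to all groups.

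**Role of MVIC.** Section 2.9 records voluntary peak torque in Nm before stimulation as a baseline measurement, and uses it as the denominator of %KEMVIT. No section lists it as an outcome at week 3 or week 6.

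**The concern.** Two things go wrong together.

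First, the quantity in the title is not the quantity compared. Torque produced by a stimulator in a relaxed limb is not voluntary strength, and the plan names no voluntary measurement after training.

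Second, the trained mode may also be the measuring instrument. Section 2.9 describes modes that differ physically: the second interval is 24 Hz at 83% amplitude in Rest mode, and 50 Hz at 100% amplitude after a 2-second gap in ON2 mode. The Hypothesis section expects the modes to affect elicited torque differently. If each group is tested in its own mode, a mode that gives more torque while switched on would show a higher value at weeks 3 and 6 even if training did nothing. An immediate effect in the opposite direction could hide a real training benefit.

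**Working it through.** **1. Structure.** Let A be the immediate difference in elicited torque between two modes and T the difference due to training. If each group is tested in its allocated mode:

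- difference at t0 (if measured) = A
- difference at week 3 or week 6 = A + T (with T taken at that visit)
- difference in change from t0 = (A + T) − A = T, provided A is additive and stable over time
- follow-up difference adjusted for the t0 value by ANCOVA = T + (1 − ρ)A, where ρ is the t0-to-follow-up correlation and the variances are equal

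**2. Inputs.** Total 66 (abstract), so 66/3 = 22 per group if equal. With 10% dropout (section 2.7), 22 × 0.9 = 19.8, or about 20 completers. SD 2.5 and alpha 0.05 come from section 2.7; a two-sided test is assumed. The protocol gives neither A nor ρ, so both are assumptions. The value 1.5 is borrowed from the sample-size target in 2.7 only to set a scale.

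The stated 66 does not follow from the section 2.7 inputs by a two-group formula: 2 × (2.5 × (1.960 + 0.842)/1.5)² = 43.6, or 44 per group. That is a separate matter, and nothing below depends on it.

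**3. Unadjusted comparison with T = 0.** For a two-sample t-test with n = 20 per arm, df = 38, the critical value is 2.024 and the noncentrality is (A/2.5) × √(20/2).

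| Assumed A | A/SD | Noncentrality | Probability of p < 0.05 |
|---|---|---|---|
| 0 | 0 | 0 | 5% |
| 0.75 | 0.3 | 0.95 | 15% |
| 1.5 | 0.6 | 1.90 | 46% |
| 2.5 | 1.0 | 3.16 | 87% |

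Masking works the same way: with A = −1.5 and T = +1.5 the expected difference is 0, and significance falls to about 5%.

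**4. If an in-mode t0 value exists.** Simulation (4,000 trials per setting, A = 1.5, T = 0, 20 per arm):

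| Analysis | ρ = 0.5 | ρ = 0.8 |
|---|---|---|
| Change from t0 | about 5% | about 6% |
| ANCOVA on t0 | 17% (bias 0.75) | 9% (bias 0.30) |

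The change score removes A up to simulation error. ANCOVA leaves (1 − ρ)A: 0.5 × 1.5 = 0.75 and 0.2 × 1.5 = 0.30.

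**5. Is that t0 value taken?** The abstract (Methods) implies that it is. The baseline list in section 2.4 does not name it. The Figure 1 caption lists a t0 time point without saying which measurement belongs to it. No change contrast is stated.

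**6. Who is tested in which mode?** One reading of section 2.9 has every participant tested in all three modes, which would allow A and T to be estimated separately. It conflicts with the abstract and section 2.5, where each participant receives one mode.

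**7. Denominator.** Section 2.9 does not say whether %KEMVIT at week 3 uses that visit's MVIC or the baseline one. As an illustration, suppose elicited torque in Nm is unchanged and MVIC rises by 14.0% or 48.5%, the range of strength gains cited in the Introduction. A same-visit denominator then multiplies %KEMVIT by 1/1.14 = 0.88 or 1/1.485 = 0.67. A strength gain would appear as a loss.

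**The case against.** A reader might infer that the training effect cannot be isolated under any reading of the protocol. The documents do not support that. A pre-training measurement in the same mode would remove an additive immediate effect through a change score, and testing everyone in all modes would make the two effects separable. The fault is that the protocol contradicts itself on both points and states no contrast that uses either.

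A reader might also take 46% as the trial's false-positive rate. It is not. It rests on an assumed immediate difference equal to a sample-size target whose unit is given only as points, in an unadjusted t-test that section 2.10 does not name. If torque is read in the interval that ON2 and Rest share with the preset stimulus, the immediate difference could be small. Section 2.9 does not say which interval is read.

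A further objection is that the hypothesis, the aim and the primary objective concern elicited torque, so a mode that produces more of it while switched on is a true finding. That stands for the acute question. It leaves the three-week programme, the week 6 follow-up and the MVIC in the title without a matching outcome.

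The choice of contrast may be left to an analysis plan that is not shown. Which measurements are taken, and in which mode, may not: voluntary torque not recorded at follow-up cannot be recovered by analysis.

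**Conclusion.** The point holds as an outcome and test-condition defect. The MVIC question in the title and Impact paragraph has no follow-up outcome, whatever the size of the immediate mode effect. The mixing of immediate and training effects is conditional: it arises if groups are tested in their allocated mode and compared without a same-mode baseline. Under those conditions and with no training effect, significance would occur in about 15% to 87% of trials for assumed immediate differences of 0.75 to 2.5 (20 per arm, SD 2.5, two-sided 0.05), against a nominal 5%. The protocol supplies no value for that difference, so the range shows sensitivity and is not an estimate. This should be corrected before data collection.

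**What to change.** In sections 2.4 and 2.9:

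1. Reconcile the abstract (Methods) and sections 2.4, 2.5 and 2.9 on which mode or modes each participant is tested in, and on whether elicited torque is taken at t0.
2. State two contrasts. Acute: elicited torque by mode at t0. Training: voluntary MVIC in Nm at t1 and t2, adjusted for t0 MVIC. Draw the training conclusion only from the second. MVIC at t0 is taken before any stimulation, so adjusting for it carries no immediate mode effect.
3. Normalise elicited torque at every visit to the t0 MVIC, so that a strength gain does not lower the outcome.
4. Elicited torque at t1 and t2 may be reported as change from t0 under the same test condition, as supportive only.

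**Cost.** A few voluntary contractions at visits already planned, on the same dynamometer and by the procedure already described. Elicited torque at weeks 3 and 6 no longer carries the training claim. A stimulation test in one mode common to all groups is not needed for this: it would add testing, and the group trained in that mode might tolerate it better.

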**Secondary outcome measures**

The secondary objective will be to assess the degree of discomfort experienced by participants for each mode condition at the current amplitude.

[figure not shown]

## **2.5 Randomization**

Randomization will be used to determine which mode the participant will receive. The randomization sequence for our three groups of interest (Off mode, Rest mode, and On2 mode) will be computer-generated by one of the investigators who will not be involved in the volunteer recruiting the sequence will then be blocked (block sizes of 4, 6, and 8, in random order). The allocation will be hidden in sequentially numbered, sealed, opaque envelopes. The participants will be stratified by their gender (female or male).

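### Block sizes of 4, 6 and 8 do not fit three arms: the list cannot be generated as written without an unstated rule, and balance within gender strata is not guaranteed

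*Protocol*

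**What the plan says.** The abstract's Methods section describes the design: "This is a single-blinded, block-randomization controlled trial". It gives the total, "Sixty-six healthy university students will be recruited from the University of Sharjah", and the number of groups: "The volunteers will be divided into three systemically randomized experimental groups".

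Section 2.5 (Randomization) names the arms, "The randomization sequence for our three groups of interest (Off mode, Rest mode, and On2 mode", and then fixes the blocking: "the sequence will then be blocked (block sizes of 4, 6, and 8, in random order". It adds one stratification factor: "The participants will be stratified by their gender (female or male". Allocation is to be concealed in sequentially numbered, sealed, opaque envelopes.

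The protocol states no allocation ratio. It does not say how a block of 4 or 8 is divided among three arms.

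**The concern.** Permuted blocks keep arms in their intended ratio because each completed block contains every arm in exactly that ratio. This requires each block size to be a multiple of the sum of the ratio. For three equal arms, that means a multiple of three, and two of the three stated sizes are not.

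Two things are at stake.

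- **Reproducibility.** Whoever generates the list must decide which arms receive the extra slots in blocks of 4 and 8. That decision is undocumented, and different choices lead to clearly different expected arm sizes.
- **Balance within gender.** Gender is the only stratification factor, and stratification acts through balance within blocks. If the three sizes are equally frequent, two blocks in every three cannot be balanced.

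**Working it through.** **Inputs.** Three arms; block sizes 4, 6 and 8 in random order; two gender strata (all section 2.5); 66 participants (abstract, Methods). Three assumptions are mine: 1:1:1 allocation, which fits 66 = 3 × 22; 33 participants per gender; and the three block sizes drawn with equal probability.

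**Step 1: divisibility.**

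| Block size | Size ÷ 3 | Remainder |
|---|---|---|
| 4 | 1.33 | 1 |
| 6 | 2 | 0 |
| 8 | 2.67 | 2 |

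Filled as evenly as possible, a block of 4 is 2:1:1 and a block of 8 is 3:3:2.

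**Step 2: would an unequal ratio rescue the scheme?** For a fixed integer ratio a:b:c to fit every block, a + b + c must divide 4, 6 and 8. Their greatest common divisor is 2, but a three-arm ratio sums to at least 3. So no fixed ratio fits all three; 2:1:1, for example, fits 4 and 8 but not 6. This result does not depend on the 1:1:1 assumption.

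**Step 3: expected arm sizes if the surplus always goes to the same arms.** One block of each size holds 4 + 6 + 8 = 18 participants, divided as follows:

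- favoured arm: 2 + 2 + 3 = 7
- second arm: 1 + 2 + 3 = 6
- third arm: 1 + 2 + 2 = 5

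Scaled to 66: 66 × 7/18 = 25.7, 66 × 6/18 = 22.0 and 66 × 5/18 = 18.3. Simulation gives 25.7, 21.9 and 18.4; the small differences come from simulation error and the incomplete last blocks.

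**Step 4: simulated arm sizes.** 10,000 lists per scheme, with 33 per gender. The gap is the largest minus the smallest arm.

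| Scheme | Mean gap | Gap of 4 or more | Exactly 22/22/22 |
|---|---|---|---|
| 4/6/8, surplus placed at random | 3.0 | 34% | 8% |
| 4/6/8, surplus to the same arms | 7.4 | 97% | under 0.1% |
| 3/6/9 | 1.1 | 2% | 47% |
| Simple randomisation | 8.0 | 86% | 1% |

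Within a single gender stratum, the gap is 3 or more in about 29% of cases with 4/6/8 and random surplus, against about 1% with 3/6/9. The imbalance left under 3/6/9 comes only from the incomplete last block in each stratum.

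**Step 5: what this costs in precision.** With a common standard deviation, the variance of a pairwise difference is proportional to 1/n₁ + 1/n₂. With 22 per arm this is 2/22 = 0.0909.

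For the fixed pattern 25.7/21.9/18.4:

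- 1/25.7 + 1/21.9 = 0.0846
- 1/25.7 + 1/18.4 = 0.0933
- 1/21.9 + 1/18.4 = 0.1000

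The average is 0.0926, so average efficiency is 0.0909/0.0926 = 98%. For the two smaller arms it is 0.0909/0.1000 = 91%.

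For random surplus, a gap of 4 such as 24/22/20 gives an average of (2/3)(1/24 + 1/22 + 1/20) = 0.0914. Efficiency is then 0.0909/0.0914 = 99.4%. Averaged over the simulated lists, it is 99.5%.

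**The case against.** The strongest case on the other side is that the defect does little harm. Surplus slots placed at random favour no arm, so the comparison stays unbiased. The arms remain much closer in size than under simple randomisation (mean gap about 3 against about 8), and the precision lost is about 0.5%. Even a fixed surplus pattern leaves a valid randomised comparison with unequal arms. All of this stands, and it limits how serious the point is.

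It is also fair that 1:1:1 is inferred and not written. The figures of 22 per arm and the simulated gaps rest on that inference; the divisibility result does not.

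A reader might infer more than the documents support:

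- **That balanced arms are impossible.** They are not: exact balance arises by chance in about 8% of lists with random surplus. What is lost is the guarantee.
- **That arm sizes will end far from 22.** This fits only the fixed pattern, and the protocol does not say that such a pattern will be used.
- **That the software would reject these sizes, or that they were carried over from a two-arm trial.** The protocol says only that the sequence is computer-generated. It names no randomisation software and gives no origin for the sizes.

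None of this supplies the missing rule. A statistical analysis plan would not normally do so either, because section 2.5 itself fixes the sizes and the list must exist before allocation starts.

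**Conclusion.** The point holds as a specification error that should be fixed. Section 2.5 combines three arms with block sizes that no fixed three-arm ratio fits. The list cannot be reproduced from its description, and balance within gender strata is not guaranteed. This conclusion needs no assumption beyond the protocol text.

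Its size rests on the assumed 1:1:1 ratio, 33 per gender and equally likely block sizes. On that basis random surplus slots roughly triple the mean gap between arms (about 3.0 against 1.1 with 3/6/9), and a fixed pattern shifts the expected arm sizes to about 26/22/18. The average efficiency loss is about 0.5% and about 2% respectively. There is no ground for calling the treatment comparison biased or the trial materially underpowered for this reason.

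**What to change.** In section 2.5, state the allocation ratio (1:1:1 if that is intended). Replace 4, 6 and 8 with randomly varied block sizes that are multiples of three, and say that the sequence is generated separately within the female and male strata.

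Sizes of 3, 6 and 9 would do. Very small blocks make the last assignments easier to predict for anyone who knows the earlier ones, and section 2.6 blinds the volunteers and the statistician but not the examiner. Using 6 and 9 limits this and still gives equal arms in every completed block.

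If enrolment has not begun, the cost is a sentence of protocol text and a regenerated list. The protocol does not say whether it has. If it has, the sponsor should document how blocks of 4 and 8 were actually filled and correct the text to match.
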